### Study setting and recruitment

Members of the local Municipal Health Commission of Liangshan and the Liangshan village chiefs will help recruit participants through in-person outreach at the villagers’ residential locations. Two hundred villages in Liangshan are defined as clusters, with 20 families randomly selected from each village as the study’s target population. One adult from each family using a mobile phone with internet service will be randomly selected as the intervention participant. One village doctor from each village will be responsible for sending the HIV-related health education information to the participants living in that village. The participants can then share the information with other family members at their discretion. In this way, the research team can first examine the effects of the intervention on the participants, and then discuss the path of secondary information dissemination and the scope of the intervention.

At the beginning of the research, the researchers will confirm the eligibility of all the participants to ensure that they meet the recruitment criteria. The researchers will then introduce the research schedule and review the message delivery tools, WeChat and the Chinese Version of TikTok, with the village doctors and participants. Next, the village doctors and participants will fill out the informed consent form, on paper or electronically. Considering the villagers’ education level and illiteracy rate, the research team staff will thoroughly explain the form’s content and meaning to them before they sign it. If the villagers cannot print their Chinese names, their fingerprints will substitute as signatures.

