### Sample size calculation

The intervention and control groups are of equal size, and two-tailed hypothesis testing is assumed. The sample size is calculated using the Stata software CRCT sample size function. By setting the power = 90%, α = 0.05, and desired confidence level = 95%, the number of clusters per arm is 66, and the sample size of each arm is 1,056. Assuming a retention rate of 80% during follow-up, 20 participants are needed for each cluster, totaling 3,960 participants for the entire study.

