#### Villagers’ baseline questionnaire

Participants and their family members will complete the baseline questionnaire in person during the enrollment procedure using the online data-collecting application Interviewer. The questionnaire will be filled out in person because many local villagers are illiterate in Mandarin Chinese, and unable to fill out the questionnaire independently without the staff’s assistance.

The framework of the questionnaire includes the following: (1) Questions on HIV-related knowledge. One of the study’s primary purposes is to measure changes in HIV-related knowledge levels among residents in Liangshan. To achieve this goal, the research team designed a new questionnaire, the HIV Related Knowledge Scale, by integrating questions from the HIV Treatment Knowledge Scale and the HIV-KQ-18 Knowledge Scale to assess the participants’ comprehension of HIV-related facts, key populations, transmission, symptoms, testing options, treatments, laws, and harmful consequences. (2) Financial information such as the family’s monthly medical and living expenditures, income level, insurance information, and savings. (3) Villagers’ additional information. This includes their demographic information (e.g., marital status, education, and current occupation), clinical characteristics (e.g., blood pressure, opportunistic infections, and height/weight/body mass index), mental health, quality of life, and stigma toward HIV (Table 1).

**Table 1 Tab1:** Outcome measures and corresponding questionnaires

Outcome	Measure	Baseline survey	Follow-up survey
Prevention			
HIV knowledge	HIV Treatment Knowledge Scale [46], HIV-KQ-18 knowledge scale [47]	X	X
Condom use	Condoms use self-efficacy scale (CUSES) [48]	X	X
Substance use	Alcohol, Smoking, and Substance Involvement Screening Test (ASSIST) [49], Drug Abuse Screening Test (DAST-10) [50]	X	X
Health outcomes			
Clinical characteristics (BMI, opportunistic infections, blood pressure)	Original measure	X	X
HIV prevalence	Regional data	X	X
Mental health	Primary Care Evaluation of Mental Disorders (PRIME-MD) patient questionnaire [51]	X	X
Quality of life	EQ-5D [52]	X	X
All-cause mortality	Regional data	X	X
Social factors			
Stigma towards HIV	Internalized AIDS-Related Stigma Scale [53]	X	X
Social support	Medical Outcomes Study Social Support Survey (MOS-SS) [54]	X	X
Evaluation of intervention and doctor			
Secondary transmission of knowledge	HIV Treatment Knowledge Scale [46], HIV-KQ-18 knowledge scale [47]	X	X

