### Outcomes measures

#### Primary outcomes

One of the study’s primary outcomes is HIV-related knowledge improvement, which is obtained by calculating weighted scores for the indicators in the HIV Related Knowledge Scale to represent the participants’ and their family members’ level of knowledge measured by the baseline and follow-up questionnaires. The research team will compare the control group and the two intervention groups to investigate whether the groups receiving the mobile-based HIV-related health education develop a deeper understanding of HIV-related knowledge than the control group which did not receive the intervention. For the second primary outcome, the research team will compare “Intervention A” and “Intervention B” to determine what type of financial reward, standardized compensation or participant performance-based compensation, is more effective at incentivizing village doctors to deliver and promote the content of the intervention. The difference between the cost-effectiveness and the participants’ HIV-related knowledge improvement of the two groups will be used to evaluate which intervention yields a more effective outcome.

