#### Secondary outcomes

Effectiveness of secondary knowledge transmission from the participants to their family members will be determined. The research team will compare the path of knowledge dissemination directly to the participants and the path of secondary knowledge transmission to their family members; measure the attenuation, weakening, errors, and gaps in the retelling and sharing of knowledge; and assess the participants’ willingness to share the knowledge with their family members voluntarily. The research team will first compare the family members’ scores from the HIV-related knowledge follow-up questionnaires to that of their previous baseline questionnaire to identify any knowledge improvement, then compare the family members’ magnitude of improvement to that of the participants’ to identify weakening and gaps in knowledge sharing.

Behavioral changes (e.g., condom use and substance use), health outcomes (e.g., clinical characteristics, HIV prevalence, mental health, quality of life, and all-cause mortality), and social factors (e.g., stigma toward HIV and social support) will be measured by the instruments outlined in Table 1. The regional data on HIV prevalence and all-cause mortality will be obtained from the local health committee.

Feasibility of the intervention will be calculated by dividing the number of people who can use WeChat and the Chinese Version TikTok by the total number of people living in the area. These data will be collected during field studies before the experiment, where the research team will randomly distribute surveys in each village to inspect the local wireless network coverage and use of mobile phones.

Level of engagement will be measured by an original engagement and attendance scale. Participants will choose from a range of 1 to 6, with 1 representing non-engaging and 6 representing highly engaging.

Acceptability and satisfaction with the intervention will be assessed via an original questionnaire with rating scales. Participants will be asked to rate and provide feedback on the intervention’s content and method, including the effectiveness of the HIV-related knowledge modules, the time and method of information delivery, village doctors’ attitude and competence, the design of the entire experimental intervention process, and more.

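### The first primary outcome includes family members without saying whether they enter the primary test, although the sample size and the A-versus-B comparison rest on enrolled participants only

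*Protocol article*

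**What the plan says.** All references are to the protocol article.

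- **Primary outcomes.** The first primary outcome is knowledge improvement, from weighted scores on the HIV Related Knowledge Scale "to represent the participants’ and their family members’ level of knowledge measured by the baseline and follow-up questionnaires". It is compared between the control group and the two intervention groups. For the second primary outcome (Intervention A against B), cost-effectiveness and "the participants’ HIV-related knowledge improvement of the two groups will be used to evaluate" which payment scheme does better. Family members are not mentioned there.
- **Study setting and recruitment.** "One adult from each family using a mobile phone with internet service will be randomly selected as the intervention participant". For everyone else in the household: "The participants can then share the information with other family members at their discretion". The same section says that effects on participants will be examined first and the path of onward transmission afterwards.
- **Villagers' baseline questionnaire and Follow-up surveys.** "Participants and their family members will complete the baseline questionnaire in person during the enrollment procedure", and both are surveyed again at 6, 12 and 18 months. The number of relatives per family is not given.
- **Secondary outcomes.** "Effectiveness of secondary knowledge transmission from the participants to their family members will be determined". The method is: "The research team will first compare the family members’ scores from the HIV-related knowledge follow-up questionnaires to that of their previous baseline questionnaire", followed by a comparison of relatives' improvement with that of participants. Table 1 lists the same two knowledge scales for this outcome as for HIV knowledge.
- **Sample size calculation.** 66 clusters and 1,056 people per arm for 90% power; with 80% retention, "20 participants are needed for each cluster, totaling 3,960 participants for the entire study".

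**The concern.** The definition of the first primary outcome names two groups with different exposure. Participants receive the messages directly; relatives learn only what a participant chooses to pass on. The protocol itself expects loss on the way, since the secondary outcome is meant to measure attenuation and gaps in retelling.

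The text does not say which group carries the test. Three readings are open: participants only, participants and relatives in one analysis, or two separate analyses both called primary. They answer different questions. A pooled analysis would estimate a blend of direct and second-hand effect. If each respondent counts equally, the weights of that blend depend on how many relatives answer, and the article does not fix that number. With two separate analyses, nothing says which one decides. Left open, the choice of primary population could be made after results are seen, and the stated power may not belong to the analysis that is run.

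**Working it through.** **1. Whom the sample size counts.** From Sample size calculation:

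- 1,056 / 66 = 16 analysed per village
- 16 / 0.80 = 20 enrolled per village
- 20 × 66 × 3 = 3,960 in total

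The chain reproduces exactly. With 20 families per village and one adult from each, it counts one person per family and no relatives. If one relative per family were added, the analysed number would be 1,056 × 2 = 2,112 per arm; with two, 1,056 × 3 = 3,168. The 66 clusters cannot be re-derived, because the article gives no effect size, SD or ICC. That is not evidence that 66 is wrong.

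**2. What pooling would do to power.** The inputs below are assumptions, since the article gives none of them: village ICC 0.05, household correlation 0.3, k relatives per family, relatives gaining a fraction f of the participants' effect, equal weight per respondent, equal variance in both groups. Taken from the article: m = 16 families analysed per village, two-sided α = 0.05, and 90% power for participants only.

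Share of the direct effect that remains: s = (1 + k·f) / (1 + k).

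Variance of a village mean, in units of the individual variance:

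- Participants only: v0 = [1 + 15 × 0.05] / 16 = 1.75 / 16 = 0.1094
- Pooled, with h = 1 + k people per family: v = [1 + (h − 1) × 0.3 + 15 × h × 0.05] / (16 × h)
 - k = 1: v = (1 + 0.3 + 1.5) / 32 = 0.0875; √(v0/v) = √1.25 = 1.118
 - k = 2: v = (1 + 0.6 + 2.25) / 48 = 0.0802; √(v0/v) = √1.364 = 1.168

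Power = Φ(3.2415 × s × √(v0/v) − 1.96), where 3.2415 = 1.96 + 1.2816 corresponds to the planned 90%.

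Example, k = 1 and f = 0.5: s = 0.75; 3.2415 × 0.75 × 1.118 = 2.718; Φ(0.758) = 0.78.

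| Fraction f gained by relatives | s, one relative | Power, one relative | s, two relatives | Power, two relatives |
|---|---|---|---|---|
| 0 | 0.50 | 44% | 0.33 | 24% |
| 0.25 | 0.625 | 62% | 0.50 | 47% |
| 0.50 | 0.75 | 78% | 0.67 | 71% |
| 0.75 | 0.875 | 89% | 0.83 | 88% |
| 1.00 | 1.00 | 95% | 1.00 | 97% |

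**3. Break-even.** Power stays at 90% when s × √(v0/v) = 1. For one relative, s = 1 / 1.118 = 0.894, so f = 2 × 0.894 − 1 = 0.79. Below about 79% transmission, pooling costs power in this setting; above it, the extra respondents more than repay the dilution.

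**4. Sensitivity.** Over ICC 0.01 to 0.20, and household correlation from the ICC up to 0.5:

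| f | Power, one relative | Power, two relatives |
|---|---|---|
| 0 | 39–57% | 20–38% |
| 0.25 | 55–77% | 40–70% |
| 0.50 | 71–90% | 62–91% |
| 0.75 | 83–96% | 80–98% |
| 1.00 | 92–99% | 92–100% |

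**The case against.** A reader might infer that the primary analysis pools participants and relatives, that the trial is therefore underpowered, and that the primary outcome duplicates a secondary one. The documents do not support any of these as fact.

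- **Pooling is not stated.** The sentence says how scores are formed and for whom, not that they enter one test. Study setting and recruitment sets a staged order, participants first and transmission afterwards, and Table 1 lists HIV knowledge and secondary transmission as separate outcomes. This stands, and it is why the point is an unresolved definition and not a proven dilution.
- **Duplication is too strong.** The secondary outcome compares relatives with their own baseline and then with participants; the primary compares arms. The scores are shared, the contrasts are not. This stands.
- **Different populations need not be an error.** A household-level effect with spillover is a legitimate target, and reaching family members is one of the stated objectives. This stands in principle, but the article does not declare such a target, and its sample size counts one person per family.
- **The power loss rests on assumptions.** This stands: with strong transmission, power holds or rises. The Sample size calculation also does not name the outcome behind the 90%, so its link to participants is inferred from the head count.
- **Analysis populations are often left to the SAP.** That would excuse silence. Here the article is not silent: it names family members in the primary definition, and that wording conflicts with its other sections.

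**Conclusion.** The concern holds as an ambiguity and an internal inconsistency. The first primary outcome names family members without saying whether they enter the primary test, while the recruitment plan, the sample size and the second primary outcome all rest on enrolled participants, and relatives' knowledge has its own secondary outcome. This can be read from the text whatever the ICC or the transmission rate.

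The effect on power is conditional on pooling and on how much relatives learn. In the base case with one relative per family, it runs from a severe loss at no transmission to a slight gain at full transmission, with break-even near 79%. It should be cited as a range, and not as the power of this trial. The correction should be made: it is cheap, and it settles the population of the main test before results are known.

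**What to change.** State in Primary outcomes that the first primary outcome is the knowledge score of the enrolled participants (one adult per family, 20 per village). This agrees with the recruitment plan, the sample size and the A-versus-B comparison. Move family members' scores wholly to the secondary transmission outcome, and add there a comparison of relatives between randomised arms to the planned comparisons with their own baseline and with participants.

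The cost is one sentence in the primary definition and one in the secondary. Data collection is unchanged and all scores are still used. The small downside is that any household-level effect is then reported as secondary. If the sponsor does want a household-level primary effect, the article should say so, fix which relatives count and how they are weighted, and size the trial for it.

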#### Secondary outcomes

Effectiveness of secondary knowledge transmission from the participants to their family members will be determined. The research team will compare the path of knowledge dissemination directly to the participants and the path of secondary knowledge transmission to their family members; measure the attenuation, weakening, errors, and gaps in the retelling and sharing of knowledge; and assess the participants’ willingness to share the knowledge with their family members voluntarily. The research team will first compare the family members’ scores from the HIV-related knowledge follow-up questionnaires to that of their previous baseline questionnaire to identify any knowledge improvement, then compare the family members’ magnitude of improvement to that of the participants’ to identify weakening and gaps in knowledge sharing.

Behavioral changes (e.g., condom use and substance use), health outcomes (e.g., clinical characteristics, HIV prevalence, mental health, quality of life, and all-cause mortality), and social factors (e.g., stigma toward HIV and social support) will be measured by the instruments outlined in Table 1. The regional data on HIV prevalence and all-cause mortality will be obtained from the local health committee.

Feasibility of the intervention will be calculated by dividing the number of people who can use WeChat and the Chinese Version TikTok by the total number of people living in the area. These data will be collected during field studies before the experiment, where the research team will randomly distribute surveys in each village to inspect the local wireless network coverage and use of mobile phones.

Level of engagement will be measured by an original engagement and attendance scale. Participants will choose from a range of 1 to 6, with 1 representing non-engaging and 6 representing highly engaging.

Acceptability and satisfaction with the intervention will be assessed via an original questionnaire with rating scales. Participants will be asked to rate and provide feedback on the intervention’s content and method, including the effectiveness of the HIV-related knowledge modules, the time and method of information delivery, village doctors’ attitude and competence, the design of the entire experimental intervention process, and more.

Retention of HIV-related knowledge will be measured by the HIV-related knowledge questionnaire. The research team will ask all participants to complete the questionnaire every 6 months after the intervention period and compare their new scores with their previous scores to examine their ability to recall information from the educational modules.

Direct and indirect costs involving each experimental group will be calculated by the research team to examine the study’s cost-effectiveness. Direct cost involves labor costs, research-related travel expenses, and village doctors’ and participants’ financial compensation. Indirect cost consists of participants’ time spent learning new knowledge and expenses on cell phone internet data.

Additionally, a semistructured individual qualitative exit interview with 20 randomly selected participants will be administered after the intervention to gather more in-depth descriptions of participants’ experiences, acceptability, and satisfaction with the intervention. They will provide an overall rating of (1) the study, (2) satisfaction with each of the study's procedure, (3) helpfulness of communication with village doctors, and (4) willingness to participate again in a similar study.

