The study has several objectives. First, to improve Liangshan residents' knowledge, attitudes, and practices regarding HIV/AIDS. Second, to determine the effect of monetary compensation on incentivizing village doctors’ dissemination of information. Third, to evaluate the path of secondary knowledge transmission from direct participants to their family members. Fourth, to test the efficacy, accessibility, convenience, and participants’ satisfaction towards the mobile-delivered intervention. Lastly, to evaluate how social, economic, cultural, cognitive, and behavioral factors influence information dissemination and comprehension, resulting in various effects of the intervention.

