### Intervention modules

The experimental intervention method involves delivering mobile-based HIV-related messages in the form of texts, pictures, audio, and videos using WeChat and the Chinese Version of TikTok to improve the villagers’ HIV-related health literacy and protect them from AIDS infection.

The “Control” group participants will not receive the mobile-based intervention delivered by WeChat and the Chinese Version of TikTok. They will receive general disease-related information from the AIDS public health campaign and mass media such as TV, newspapers, and internet.

In addition to receiving general information from mass media and campaigns, the participants in the “Intervention A” and “Intervention B” groups will receive HIV/AIDS awareness-raising and behavior-related cyclical messages delivered by the village doctors on a biweekly basis for 18 months. Participants who are illiterate in Mandarin Chinese or have difficulty understanding the content of the messages can consult their village doctors on WeChat in the village group chat or in a private one-on-one conversation. They may request a translation of the message into the Yi ethnic group’s language or ask the doctor to clarify and explain its content.

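### Secondary transmission is judged only by comparing family members' and participants' knowledge gains, which cannot separate not sharing from loss in retelling or from learning elsewhere; willingness to share has no named measure

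*Protocol article*

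**What the plan says.** The objectives at the end of the Background include "to evaluate the path of secondary knowledge transmission from direct participants to their family members". The Secondary outcomes section turns this into three tasks. One is to compare the direct path with the path through the participant. Another is to "measure the attenuation, weakening, errors, and gaps in the retelling and sharing of knowledge". The remaining task concerns voluntary sharing, where the stated aim is to "assess the participants’ willingness to share the knowledge with their family members voluntarily".

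The same paragraph then gives the procedure in two steps. The team will "first compare the family members’ scores from the HIV-related knowledge follow-up questionnaires to that of their previous baseline questionnaire", and "then compare the family members’ magnitude of improvement to that of the participants’ to identify weakening and gaps in knowledge sharing".

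In Table 1, the row "Secondary transmission of knowledge" lists the HIV Treatment Knowledge Scale and the HIV-KQ-18 and nothing else. Other rows of that table, such as feasibility, engagement and acceptability, show a purpose-made measure where one is planned.

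Two further statements matter. On sharing, Study setting and recruitment says: "The participants can then share the information with other family members at their discretion". On background information, Intervention modules says of the control participants: "They will receive general disease-related information from the AIDS public health campaign and mass media such as TV, newspapers, and internet". The intervention arms receive the same general information in addition to the messages.

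**The concern.** A knowledge score records how much a person knows. It does not record whether the participant passed anything on, what was passed on, or from whom the family member learned. Since sharing is optional, whether it took place is unknown in every household unless someone asks.

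The second step nevertheless attaches a meaning to the score difference: a smaller gain in family members is taken to show weakening and gaps in sharing. That conclusion needs sharing to have happened and the participant to have been the source. If participants mostly did not share, the lesson for a later programme is to encourage sharing. If they shared and the content degraded, the lesson is to make the messages easier to retell. If family members learned elsewhere, the gain says nothing about transmission. The Discussion presents secondary transmission as one of the study's strengths, so the distinction is worth making.

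**Working it through.** The document gives no figure for this outcome, so there is none to reproduce. The check has two parts.

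**1. Is sharing recorded anywhere in the listed measures?**

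- Table 1, secondary transmission: two knowledge scales only.
- Villagers' baseline questionnaire: knowledge, finances, demographics, clinical characteristics, mental health, quality of life and stigma. No sharing item is listed.
- Follow-up surveys: described as identical to baseline. Table 1 has some follow-up-only measures, but none on sharing.
- Monthly telephone interviews (Village doctor incentives and performance monitoring): the doctor's completion of tasks, understanding of key points, and satisfaction with the doctor.
- Exit interview of 20 participants: experience, acceptability and satisfaction, with four rating topics. None concerns sharing with family.

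No listed source asks whether, what or how often participants shared, how willing they were, or where family members learned.

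**2. Can the planned comparison separate the explanations?**

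Write the family members' average gain as F = s·r·G + b, where

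- G is the participants' gain,
- s is the proportion of participants who pass content on,
- r is the fraction of content that survives retelling,
- b is the family gain from campaigns, mass media or repeated testing, taken as equal in all arms.

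All values below are assumed, with G = 20 points on the 1 to 100 scale. The last column assumes that control families gain b only.

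| Case | s | r | b | F = s·r·20 + b | F/G | F − b (net of control families) |
|---|---|---|---|---|---|---|
| All share, 60% lost | 1 | 0.4 | 0 | 8 | 40% | 8 |
| 40% share, nothing lost | 0.4 | 1 | 0 | 8 | 40% | 8 |
| Half share, 20% lost | 0.5 | 0.8 | 0 | 8 | 40% | 8 |
| Half share, 60% lost, some background | 0.5 | 0.4 | 4 | 4 + 4 = 8 | 40% | 4 |
| Nobody shares | 0 | not applicable | 8 | 8 | 40% | 0 |

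The planned comparison returns 40% in all five cases. Subtracting the control families' gain separates the last two cases from the rest, because it removes b. It does not separate the first three, since only the product s·r is left.

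If intervention-arm families also learn directly from the doctor or the study videos (a gain d), the net figure becomes s·r·G + d. For example, 0.5 × 0.4 × 20 + 4 = 8, the same as in the first three cases. So the control contrast gives a total effect on family members and does not identify the route.

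**The case against.** The strongest reply is that a journal article condenses the full protocol, and that item-level questionnaire content is the kind of thing it leaves out. The questionnaires do collect more than Table 1 shows: finances and demographics have no row there. Content is to be adjusted after piloting, and the Abstract says the outcomes will be explored by both qualitative and quantitative means. This carries weight for willingness, which has its own clause. A reader might infer that willingness will be read off the family members' scores, but no section says so. All that can be said is that no measure is named for it. The reply does not cover the transmission comparison, because there the article names the instrument, the two steps and the reading of the result.

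Three further replies are partly right:

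- **The control contrast.** A reader might infer that the scores cannot show whether the messages reached families at all. The Primary outcomes section includes family members' scores in the knowledge outcome that is compared with control. These data can show reach into households beyond campaigns, media and retesting.
- **Domain scores.** The domains of the knowledge scale follow the eight message modules. Comparing participant and family member by domain can partly show which content is missing or wrong.
- **Household distributions.** Half the households sharing everything and all households losing half give the same mean but different spreads across households. The data carry some information on this, though with noise.

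None of the three shows who shared, how willingly, or from whom the family member learned.

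A reader might also put a size on the error. If a share q of family gain came from other sources, transmission would be overstated by 1/(1 − q): 1/0.75 = 1.33 at 25%, and 1/0.50 = 2 at 50%. The document gives no such shares, and much of this excess would be removed by the control contrast. It also requires only doctors and participants to follow the video accounts, and gives no sign of how much family members learn from them directly.

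**Conclusion.** The point holds in a limited form. The stated comparison of family gain with participant gain cannot separate not sharing from loss in retelling, and it cannot identify the source of family members' knowledge. It therefore does not answer the objective on the path of transmission, and a shortfall should not be reported as weakening in sharing on that evidence alone. Willingness to share has no named measure.

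The size cannot be computed from the document. The 8-point illustration rests on assumed values and shows only that different explanations give the same result. The conclusion also rests on the measures as listed: if the full questionnaires already contain sharing and source items, the remedy is to name them and tie them to the analysis. The point concerns one secondary outcome. The primary comparisons are not affected.

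**What to change.** **Items.** Add a few short questions at the end of the existing follow-up questionnaires, after the knowledge scale so that they cannot influence it, and in all three arms.

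- Participants: whether they shared HIV information with the family member, how often, and on which modules (worded by topic, so that the question also works in the control arm).
- Family members: where they learned about HIV, with the participant, the village doctor, videos seen directly, campaigns or media, and other as options.

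**Analysis.**

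- Report the proportion who shared as the measure of willingness.
- Take the between-arm contrast of family members' change in score, allowing for clustering by village, as the effect on family members.
- Report the participant-to-family difference by module among households that report sharing. Label it observational, because sharing is a behaviour that arises after randomisation.
- Drop the reading of any overall shortfall as weakening in sharing.

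**Cost.** A few minutes per survey in visits already planned for both groups, plus revised analysis wording. There are two drawbacks. Self-report may overstate sharing. Asking at 6 and 12 months may itself prompt sharing and so change what is being measured. Asking the sharing items only at 18 months limits the second problem, at the price of longer recall.
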